##### Exclusion criteria

Females, patients with a concurrent alternate lower limb diagnosis, those on anticoagulant medication or having had previous tendon surgery or injection to the affected limb will be excluded. Plantaris involvement in Achilles tendinopathy will be treated as an alternate lower limb diagnosis as this is associated with resistance to conservative treatment and surgery may be more appropriate [27]. Tears and partial tears will also be treated as alternate diagnoses.

### Follow up

Outcome measures will be taken at baseline and at 6 weeks and 3, 6 and 12 months follow up.

### Primary endpoint/outcome

The Visual Analogue Scale (VAS) for pain on day of review at 6 months.Validated Victoria Institute of Sport Assessment-Achilles (VISA-A) [28] and Victoria Institute of Sport Assessment-Patella (VISA-P) [29] scores for pain and function at 6 months.

The 5RM provides an objective marker for load capacity of a certain muscle group. Limitation of this test is that weight can only be added by increments that the machine allows (5Kg/heel raise, 2.5Kg/knee extension). Machine is standardised for every test. Decision to use machines rather than test with free weights is primarily based on safety. Ideally Isokinetic testing would be preferred but is not available

#### Procedure (Table 5)

**Table 5 Tab5:** Patient timeline (Spirit Figure)

	Study period						
	Enrolment	Allocation	Post-allocation				Close-out
Timepoint	Referral from RRU	First clinic	6w	3m	6m	12m (remote)	
Enrolment:		X					6m clinic, 12m remote
Eligibility screen	X	X					
Informed consent	Written info sent	X					
Allocation/Random		X					
Interventions:							
*RCT Injection*		X					
*Progressive Exercise Loading Programme*		X	X	X	X	X	
Assessments:							
*Epidemiology Questionnaire*		X					
*VISA, VAS, FAA,*		X	X	X	X	X	
*USS, Ohberg*		X	X	X	X		
*Strength/ Small Knee Bend*		X	X	X	X		
*Adherence to Rehabilitation Programme*		X	X	X	X		

As testing and interventions outlined in this study may be delivered to eligible participants at the first appointment information will be sent in advance. This will be done by post providing information sheets. Eligible patients will be asked to complete the informed consent form at the first appointment with the consultant performing the intervention. Ineligible patients will continue to be treated as per current guidelines as will those that decline study participation.

During the follow up period all participants will be advised to continue with a home exercise programme. Physiotherapy treatment will continue at primary care and Regional Rehabilitation Unit (RRU) level as required. Oversight of this will be maintained by the lead physiotherapist at Defence Medical Rehabilitation Centre (DMRC) Headley Court by providing instruction to primary care and RRU physiotherapists directly to ensure standardisation of post intervention physiotherapy. All participants will be progressed along an incremental pathway of rest, isometric, isotonic, EL/HSR and then sport specific activity including plyometrics as per Table 2. Participants will be asked to refrain from seeking alternative treatments during the trial and to complete an exercise logbook specific to this study.

#### Randomisation and blinding procedures

One hundred and eight participants (see power calculation below) will be allocated in equal proportions across the 3 intervention arms. 12 batches of 9 envelopes numbering 108 envelopes in total with 36 pertaining to each arm of the study will be prepared and secured in a locked container held centrally at DMRC. In this manner should the recruited numbers differ participants will be randomly allocated whilst the proportion of numbers across all 3 arms will be equal throughout the data collection phase.

Once participant eligibility and informed consent are confirmed, an independent administrator will open one of the batched envelopes to assign the participant to one arm of the trial. The treating clinicians including physiotherapists and consultants delivering injection interventions will be blinded to which of the three injections they deliver. The Chief Investigator will be informed of which participants are involved in each trial arm and responsible for preparation of injection syringes checked by a nurse or other doctor not involved in the trial. The reception staff will direct participants to a separate area in the waiting room where they will be able to complete VAS, VISA and FAA questionnaires in private. The reception staff will check the questionnaires for basic errors (eg a missed page) before filing this in a locked store. The study administrator will collate these outcome measures on a spreadsheet designed by the Chief Investigator this will be kept in a locked store and backed up electronically in a password protected Microsoft Excel file on the Defence computer network. The Chief Investigator will store hard copies of the outcome measures in the locked Academic Department of Military Rehabilitation (ADMR) store and update a second outcomes spreadsheet so that double data entry is achieved. A separate store with a list containing the consecutive trial numbers 1–108 ascribing those numbers to patient notes numbers and which trial arm they are in will be maintained by the Chief Investigator and secured in a locked store within the ADMR. A second copy of this list will be continually updated and provided to the Independent Medical Officer who will store this list in a locked store. This is so that in case of emergency either the Chief Investigator or Independent Medical Officer could be contacted to confirm which treatment a participant had been given. The DMRC Pharmacy will also retain hard copies of individual prescriptions as well as the prescriptions log.

Fully blinding the control injection arm to the clinician is not possible due to the small volume of injectate (3ml of LA) and difference in procedure; neovessels will not be targeted under US guidance. The two treatment arms will be fully blinded to both clinician and participants, as the volumes delivered will be equal and technique identical. The steroid to be used does not appear opaque in the syringe maintaining clinician blinding. Clinicians and participants will be shielded from syringe preparation. To assess blinding at trial completion participants will be asked if they think they were randomised to any individual trial arm, if they think they received either a HVIGI or control or if they don’t know which injection they received.

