### Sample size

The effect size *f* has been calculated along with the overall predicted sample size calculation using GPower (University of Dusseldorf, GER) [33]. The Minimum Clinically Important Difference (MCID) in the VISA-P score in athletes with patellar tendinopathy who underwent conservative management was calculated by Hernandez-Sanchez [34] to be 12.6 (*n* = 90 baseline VISA-P = 50.1 (SD = 18.4). The effect size *f* of 0.3228096 was combined with an α-level of 0.05 and power of 0.8 in a priori power calculation for an ANOVA, fixed effects, omnibus one way test predicting an initial sample size of 96. The calculation was repeated so that addition of a suspected covariate (percentage adherence to the standardised rehabilitation protocol) could be considered in ANCOVA again a sample size of 96 was predicted. Further calculations were made to allow using repeated measures, between factors ANOVA assuming correlation of 0.5 among repeated measures this returned a smaller total sample sizes of 75 for primary outcome measures (baseline and 6 month follow-up) and 60 for secondary outcome measures (baseline, 6 weeks, 3,6 and 12 month follow-ups). 108 participants with either Achilles or patellar tendinopathy will be recruited to allow for a 10% drop out rate.

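### Tendon site decides which VISA score is used but is neither a stratum in the allocation list nor a term in the stated model, and pooling of VISA-A and VISA-P is left unstated: a modest loss, cheap to repair

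*Protocol article*

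**What the plan says.** All places are in the Protocol article.

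- **Primary endpoint/outcome.** There are two primary measures at 6 months. One is VAS pain, on the same scale for every patient. The other is "Validated Victoria Institute of Sport Assessment-Achilles (VISA-A) [28] and Victoria Institute of Sport Assessment-Patella (VISA-P) [29] scores for pain and function at 6 months", that is, one instrument per tendon.
- **Randomisation and blinding procedures.** There is one set of envelopes: "12 batches of 9 envelopes numbering 108 envelopes in total with 36 pertaining to each arm of the study". Participants "will be allocated in equal proportions across the 3 intervention arms", and the balance promised is that "the proportion of numbers across all 3 arms will be equal throughout the data collection phase". The number list is also single: "A separate store with a list containing the consecutive trial numbers 1–108". Tendon site is not mentioned.
- **Sample size.** The inputs are VISA-P only: a minimum important difference given as "to be 12.6 (*n* = 90 baseline VISA-P = 50.1 (SD = 18.4". They feed a one-way, three-group ANOVA with a total of 96. Both tendons count towards the recruited total: "108 participants with either Achilles or patellar tendinopathy will be recruited to allow for a 10% drop out rate". No tendon split is given.
- **Statistical analyses.** The model is a repeated measures ANOVA with time and intervention as factors. Rehabilitation adherence is the only covariate named. ANCOVA is kept in reserve for group differences judged to need it. Tendon site is not among the baseline factors listed.

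**The concern.** Tendon site is known before allocation and determines the measuring instrument, so it is the obvious candidate for a stratum and a model term. The plan as fixed uses it as neither. If the tendons differ in how much their VISA score changes, that difference sits in the error term of the stated model, and a chance difference in tendon mix between arms moves the treatment contrasts.

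The outcome definition is also incomplete. The article never says that VISA-A and VISA-P values go into one analysis, yet the sample size works only if they do.

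**Working it through.** **1. Reproduce the plan's figure.** Inputs from *Sample size*: difference 12.6, SD 18.4, alpha 0.05, three groups. With arm means 0, 12.6 and 12.6, the SD of the means is 12.6 × √(2/9) = 5.94, and f = 5.94 / 18.4 = 0.3228, as stated. With N = 96 the noncentrality is 96 × 0.3228² = 10.0 on 2 and 93 df. Power is 80.2%, and N = 95 gives 79.8%. The stated 96 is confirmed.

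**2. Which gap matters.** The time by intervention test compares arms on change from baseline. A fixed difference in level between VISA-A and VISA-P drops out, and only a difference in change (D) counts. Under the plan's own assumed correlation of 0.5, the SD of change is 18.4 × √(2 × (1 − 0.5)) = 18.4, so the same SD can be used for change.

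**3. What Table 1 suggests for D.** VISA gains, taking the last time point shown and the 50 ml group of the two-volume study:
- Achilles: 31.4, 38, 28.7, 32.9, 41, 33.4; mean 34.2.
- Patellar: 22, 19, 29.3; mean 23.4.
- Unweighted gap: 10.8.
- Size-weighted gap, leaving out the two-volume study because its group sizes are not given: 33.0 − 25.6 = 7.4.
- The two aprotinin series, the closest match in treatment and follow-up: 32.9 − 29.3 = 3.6.

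**4. Power without a tendon term.** Total SD = √(18.4² + p(1 − p)D²). Assumptions: Achilles share p = 0.5, within-tendon SD 18.4, N = 96.

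| D (points) | Total SD | Power |
|---|---|---|
| 0 | 18.40 | 80.2% |
| 3.6 | 18.49 | 79.8% |
| 7 | 18.73 | 78.7% |
| 11 | 19.20 | 76.5% |

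With a tendon term the residual SD stays at 18.4. The lost degree of freedom moves power only from 80.22% to 80.20%, whatever D is. If 18.4 is instead the total SD over both tendons, the term raises power, for example to 83.3% at D = 10.

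**5. Chance imbalance in tendon mix.** Take 36 per arm and 54 of each tendon, allocated without regard to tendon (hypergeometric).
- SD of the difference in Achilles share between two given arms: 11.8 percentage points.
- Probability that two given arms differ by 20 points or more: 7.8%.
- Probability that some pair of the three does: about 19%.
- Shift in a contrast from a 20-point imbalance: 0.20 × 7 = 1.4 to 0.20 × 11 = 2.2 VISA points, against a standard error of 18.4 × √(2/36) = 4.3.

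**6. Why pooling must be stated.** If each instrument were tested alone with 48 patients, the same f gives power of 47.6%.

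**The case against.** **VAS is also primary.** It is scored identically in both tendons, so the instrument problem does not touch it. This stands and limits the point to VISA.

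**The plan implies pooling.** There is one total for both tendons and one ANOVA, and no per-tendon test is proposed. A reader might infer from the naming of two scores that the VISA analysis has only about 48% power. The documents do not support that. The figure shows only why the pooling should be written down.

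**Confounding is the wrong word.** A reader might infer that arm is confounded with instrument. Allocation is random, so any difference in mix is chance. It is the same variation that enlarges the residual SD in step 4, so the shift in step 5 must not be added to the power loss as a second harm.

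**Table 1 is weak evidence that tendon is prognostic.** The series are uncontrolled, and the Background itself calls them hard to interpret. Several Achilles gains are at 3 to 4 weeks, while the patellar gains are at 12 weeks or later. The 30 ml Achilles group gained only 6.94. This stands: a gap of 7 to 11 points is a hint, and nothing in the document supports 15.

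**The article is condensed.** The baseline factors are not presented as a complete list, and the reserve ANCOVA could take in tendon. This stands in part. But the article does fix the envelope scheme, the model factors and the named covariate, and tendon is in none of them. An adjustment that depends on differences seen in the data does not replace a prespecified term.

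**Conclusion.** The point holds as a modest, nearly free improvement. Tendon site belongs in the primary model and, if still possible, in the allocation scheme, and the article should say that the two VISA scores are pooled.

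For VISA, leaving tendon out costs about 1.5 to 4 points of power (80.2% to 76.5–78.7%) and leaves about an 8% chance that a given pair of arms is 20 or more percentage points apart in tendon mix. These sizes rest on an even tendon split, a within-tendon SD of 18.4 and a gap in change of 7 to 11 points. The document gives neither the split nor the gap. At the 3.6-point gap of the aprotinin series the loss is under half a point.

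The sample size arithmetic is correct, and the absence of stratification is not itself an error.

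**What to change.** 1. Define the primary VISA outcome as the tendon-appropriate score (VISA-A for Achilles, VISA-P for patellar) at 6 months, analysed in one pooled model.
2. Prespecify tendon site as a fixed factor. If the repeated measures model is kept, include tendon by time as well, since the main effect alone does not absorb a difference in change. If ANCOVA is used, include the baseline score from the same instrument.
3. If recruitment has not begun, prepare two envelope series, one per tendon, each in batches balanced over the three arms. If it has begun, items 1 and 2 are enough.
4. Report the arm by tendon interaction and the per-tendon estimates as descriptive only.

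Cost: one or two degrees of freedom and re-sorting of envelopes. No extra patients.

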### Screening

Patients will be screened as per their normal routine care for a tertiary referral to DMRC Headley Court. They will have a 45-min initial appointment with one of the research team consultants. This will include reviewing their medical history and checking parameters such as weight, BMI, pulse and blood pressure. No more invasive tests are required.

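### Fixed batches of 9, with a consenting consultant who injects and can recognise the control, allow control versus HVIGI to be foreseen for up to about 21% of allocations

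*Protocol article*

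**What the plan says.** All places are in the protocol article.

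- **Scheme** (Randomisation and blinding procedures): participants "will be allocated in equal proportions across the 3 intervention arms", using "12 batches of 9 envelopes numbering 108 envelopes in total with 36 pertaining to each arm of the study". The stated purpose is that, even if recruitment falls short, "the proportion of numbers across all 3 arms will be equal throughout the data collection phase".
- **Opening** (same section): "Once participant eligibility and informed consent are confirmed, an independent administrator will open one of the batched envelopes". The envelopes are kept locked and held centrally.
- **Who enrols**: under Screening, "They will have a 45-min initial appointment with one of the research team consultants". Under Procedure, eligible patients "complete the informed consent form at the first appointment with the consultant performing the intervention".
- **Who injects**: Secondary endpoints/outcomes mentions three operators delivering injections, with one of them usually doing the scoring. Interventions names one clinician. Study setting gives a single centre.
- **Blinding of the injector**: Randomisation and blinding procedures first says that treating clinicians are blinded to which of the three injections they give. It then says "Fully blinding the control injection arm to the clinician is not possible due to the small volume of injectate" and because the procedure differs; only the two HVIGI arms are fully blinded. These two statements must be reconciled.
- **Access**: Blinding and data access gives treating clinicians the clinical record and the ultrasound images.

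**The concern.** With a constant batch size, anyone who can tell the allocations apart as they accumulate can work out the rest of the batch. Here the person placed to do so also sees the next patient, judges eligibility and takes consent. He cannot separate the two HVIGI arms, but control versus HVIGI is the superiority comparison in the hypotheses (Background).

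If the next allocation is known, the judgement on eligibility or the way consent is discussed can shift, and the patients entering control may then differ from those entering HVIGI. Both primary outcomes, VAS and VISA, are completed by the patient. Adjustment for measured baseline values would correct such selection only in part.

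**Working it through.** **1. The plan's own figures.** 12 × 9 = 108, and 108 / 3 = 36 per arm. The sample size of 96 inflated for 10% dropout is 96 / 0.9 = 106.7, so 107, rounded up to 108. The article's numbers agree.

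**2. Content of a batch.** Equal allocation that stays equal throughout implies 3:3:3 in each batch of 9, seen by the injector as 3 control and 6 HVIGI. This is inferred, not written. Using the batches one after another is also assumed.

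**3. Certain allocations with full knowledge.** The next class is certain once all 3 controls or all 6 HVIGI of the batch have been used. There are C(9,3) = 84 equally likely orders.

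- Expected run of HVIGI left after the last control: 6 / (3 + 1) = 1.50
- Expected run of controls left after the last HVIGI: 3 / (6 + 1) = 0.43
- Sum: 1.93 of 9 = 21.4%
- Over 12 batches: 12 × 1.93 = 23.1 of 108, made up of 12 × 1.50 = 18 HVIGI and 12 × 0.43 = 5.1 control

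Enumeration of all 84 orders gives the same total. By position in the batch:

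| Position | 1–3 | 4 | 5 | 6 | 7 | 8 | 9 |
|---|---|---|---|---|---|---|---|
| Chance that the class is certain | 0 | 1.2% | 4.8% | 11.9% | 25% | 50% | 100% |

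The row sums to 1.93. The exact arm is known only when the certain class is control: 0.43 / 9 = 4.8% of allocations.

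**4. Certain allocations with partial knowledge.** Suppose the consultant knows only the injections he gave himself. The share he gives is not in the article, so the range is an assumption (simulation, 60,000 batches per row).

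| Share of injections he gives | Certain, among his own |
|---|---|
| 100% | 21.4% (exact) |
| 95% | 17.9% |
| 90% | 14.7% |
| 80% | 9.8% |
| 70% | 6.3% |

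**5. Varied batches.** Take four batches each of 6, 9 and 12. Envelopes: 4 × (6 + 9 + 12) = 108. Per arm: 4 × (2 + 3 + 4) = 36. The order is hidden, and the guesser is assumed to know the set of sizes and every earlier allocation. Results for this scheme are simulated.

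| Measure | 12 batches of 9 | Four each of 6, 9, 12 |
|---|---|---|
| Certain allocations | 21.4% | about 4% |
| Accuracy of the best guess at every allocation | 72.8% | 71.8% |
| Accuracy of always guessing HVIGI (72 / 108) | 66.7% | 66.7% |
| Largest gap between two arms if stopped mid-batch | 3 | 4 |

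**The case against.** The case on the other side is substantial.

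- **Concealment is otherwise sound.** Envelopes are locked away and opened by an independent administrator after eligibility and consent. This protects the current envelope. It does not stop a deduction from injections already given, which needs no access to the envelopes.
- **21% is an upper value.** It needs 3:3:3 batches, sequential use, and one consultant who knows the batch size and every earlier allocation. With several operators the share is lower, as the range shows. That stands. However, one operator appears to do most of the work at the only site, and treating clinicians can see the clinical record and images.
- **Most certain allocations are of the majority class.** Of the 1.93 per batch, 1.50 are HVIGI with steroid status unknown. Varying the batch sizes lowers overall guessing accuracy by only about 1 percentage point. Both facts stand and limit the gain from the change. What it removes is mainly certainty, not informed guessing.
- **Discretion is limited.** Patients arrive by referral after failed treatment, and ultrasound criteria are listed. The article supports influence over whether a patient is enrolled. It does not describe control over when.
- **Analysis offers some protection.** Outcomes are measured at baseline, and ANCOVA is planned where groups differ (Statistical analyses). It would be wrong to say that no analysis helps, but unmeasured selection would remain.
- **Fixed blocks are a recognised choice, and the article is condensed.** The full protocol may withhold batch boundaries from clinicians. The point rests on the scheme as stated, not on that silence; still, the batch size is printed in a public article.

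A reader might infer that a fifth of allocations will be foreseen, or that the trial is biased. The documents support neither inference. They describe a scheme that makes foresight possible under the conditions listed.

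**Conclusion.** The point holds as a weakness that is cheap to reduce, not as an error. A consultant with full knowledge of earlier allocations could be certain of control versus HVIGI for up to about 21% of allocations on average, and for about 18% to 6% if he knows only his own injections and gives 95% to 70% of them. The assumptions are the inferred 3:3:3 split, sequential use of batches, knowledge of the batch size, and an injector who recognises the control. The last follows from the article's own concession, although the same section elsewhere says that injectors are blinded to all three injections. The consequence is an opening for selection in the main comparison; its effect on the result cannot be quantified from the document.

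**What to change.** Replace the unused batches of 9 with batches of varying size in random order, for example 6, 9 and 12. One set of the three sizes totals 27 and replaces three batches of 9; four sets keep the full 108 envelopes and 36 per arm. Withhold the sizes and boundaries from the consultants and physiotherapists, and state that envelopes are opened in strict numerical order. In the same revision, reconcile the two statements on whether the injector is blinded to the control.

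The cost is re-preparing the unused envelopes and a sentence or two of text. If recruitment stops mid-batch, arms could differ by up to 4 instead of 3. The figure of about 4% certain allocations applies if all 108 envelopes are replaced; batches already used stay as they were.
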